### Recruitment {15}

The six participating sites treat a total of approx. 6,000 acute stroke patients per year (~ 15,000 during the 30-months recruitment period), of which 144 patients will be included (i.e., ~ 1% of the stroke population handled at the study sites, and on average 10–11 patients per study site per year). Similar recruitment rates have been achieved in the targeted patient group previously by the applicants in pilot studies in Tübingen and Cologne [32]. All sites have long standing expertise with TMS in stroke trials and authority to fully access patients on their Stroke Units for trial recruitment. According to the Declarations of Commitment of the study sites, there is confidence that recruitment will be feasible as planned.

The following overall dropout rates (i.e., loss to follow-up for all kinds of reasons) were reported in the high-frequency rTMS trials in early subacute stroke patients with similar trial designs: 17% of 157 included patients [21], 20% of 69 patients [18], 5% of 41 patients [19], 24% of 42 patients [20], 17% of 24 patients [2]. On average, the dropout rate in these trials was 17.1%.

## Methods: assignment of interventions

### Sequence generation {16a}

Patients will be randomized to one of the three study conditions/arms (1:1:1) and will be stratified according to study center and motor threshold (≤ 60%; > 60%MSO). The biostatistical center produced a randomization list (block randomization) with varying block length and stratified for study center to realize a 1:1:1 randomization. The randomization of each participant will be conducted centrally by the biostatistical centre via electronic interaction. The operator at each center will be responsible to implement the randomized treatment set-up. Patients and raters will be blind to the rTMS condition.

### Implementation {16c}

Patients will be recruited in the participating study centers after admission due to acute ischemic stroke. Recruiting is possible from the day of admission. Patients fulfilling all inclusion and none of the exclusion criteria will be enrolled into the study. Randomization will be performed electronically via the database by any study team member other than the rater at the end of the screening visit. The randomization sequence will then be generated by the biostatistical center and will be sent to the designated operator via email.

### Concealment mechanism {16b}

The sequence consists of numbers and one letter. The number is entered in the stimulator and determines whether the active or placebo side of the symmetrical coil will be used. The letter is entered in the control software of the real-time digital signal processor and determines whether pulses are administered synchronized or non-synchronized to EEG.

## Assignment of interventions: blinding

### Who will be blinded {17a}

The patient as well as the rater will be blinded to the intervention condition the patient receives. A blinding of the medical doctor and/or study personnel conducting the intervention treatment is not possible, since setting‐up as well as controlling the intervention treatment requires knowledge of the intervention condition.

### Procedure for unblinding if needed {17b}

A randomized log is kept at the study center by the study personnel conducting the intervention treatment at the study center. This list contains patient name, patient study ID and the assigned treatment condition. The study personnel has to ensure that the log is kept at a safe place, that is accessible in case of emergency unblinding. The operator and study physicians will have access to the un-blinding list, if necessary for medical reasons. The actual allocation must not be disclosed to the patient and/or other study personnel including other site personnel, monitors, corporate sponsors or project office staff. Investigators are encouraged to discuss with the principal investigators if they believe that unblinding is necessary. Premature unblinding of study participant has to be considered in case of severe adverse events or medical emergency. The reason for unblinding, date and time, and names of the study team members will be documented on the un-blinding log. The monitor and the biostatistical center will be informed.

## Data collection and management

### Plans for assessment and collection of outcomes {18a}

Patient assessment source data will be managed following Good Clinical Practice (GCP) guidelines using an FDA-conforming database with an audit trail and internal monitoring provided by the coordinating center. Participating centers will submit data using electronic case report forms (eCRF). The name, day of the month, and month of birth of participants will not be stored electronically, participant data records will be identified with identifier unique to each participant. Corresponding personal data will be maintained in paper format by each participating center and with a copy (via fax) of forms containing the participant’s name and contact data (such as consent forms) transmitted to the coordinating center. All paper data will be maintained in a locked room and locked cabinet. The informed consent process is documented in the patient records. The original signed documents will be part of the investigator’s site file and retained with it and one copy included the insurance policy of the trial will be handed to the patient. All procedures administered to the subjects on entry to the trial or at any time during the trial will be documented paper-based in a pseudonymous manner. At the end of each visit, the data will be entered into The Clinical Data Management System [“secuTrial”], which will be used for data capture, processing and storage of study data. The paper-based documentation will be stored in a lockable cabinet at the investigational site, not-accessible to non-authorized personnel. Data entry is performed access-controlled at the investigational site by clinical staff after having received training and a user manual for the electronic CRF. Raw biosignal data will be uploaded to a secure cloud server at the coordinating center for quality control and analysis. Various EEG and EMG measures (spectral analysis, signal-to-noise ratio, motor evoked response amplitudes, etc.) will be extracted by the coordinating center and stored in the trial database.

### Plans to promote participant retention and complete follow-up {18b}

There is existing evidence that early subacute patients receiving real rTMS are likely to have a therapeutic benefit on their neurorehabilitation [7]. Patients in the Experimental Condition (personalized stimulation) will receive real rTMS stimulation. In addition, the stimulation will be personalized to their individual brain rhythm, for which the study hypothesizes a further increase in beneficial effects. Patients in Control Condition 1 (non‐personalized stimulation) will receive real rTMS. As mentioned above, there is existing evidence for a beneficial effect of real rTMS in this patient population. Patients in Control Condition 2 (sham stimulation) are not expected to benefit from the sham stimulation, however, they receive task‐specific hand‐arm physiotherapy every day until the end of the therapy visits. The beneficial rTMS effects remain to be demonstrated, however, patients have the chance to receive additional treatment beyond standard treatment that can promote the motor recovery of their paretic arm while keeping the risk of side effects particularly low. Therefore, it is expected that there will be a high level of interest and compliance on the part of patients. In terms of the follow-up visit 3 months post-intervention we offer reimbursement for travel costs including a travel‐accident insurance. Each study participant is insured against any health impairment occurring as a result of participation in the study in accordance with the applicable laws and regulations.

### Data management {19}

The trial Case Report Form (CRF) is the primary data collection instrument for the trial. For this project, electronic Case Report Forms (eCRFs) will be used. The Clinical Data Management System [“SecuTrial”] is validated and changes are tracked via an audit trail. The Center for Clinical Trials Tübingen (ZKS) will monitor the correct completion / perform plausibility checks of the data stored in the eCRFs to avoid discrepancies with the source data. Implausible or missing data will be queried. The data from all centers will be entered in a central data base (secuTrial) provided by the Institute for Clinical Epidemiology and applied Biostatistics (IKEaB, University Tübingen). The system secuTrial is validated and used by several centers for clinical trials in Germany. It is linked to the central data center of the University Hospital Tübingen (UKT) and to which only authorized staff of the IKEaB has access. The data managing plan (including digital data storing and archiving) of the IKEaB will comply with all legal requirements. The system secuTrial provides an audit trail for all activities (data entry, modification, and deletion). A role system allows access to selected patients and different rights (reading, writing) for different investigators. The IKEaB will provide an intensive training for all users of this system during the study.

The correctness of entries in CRFs will be confirmed by dated signature of an authorized investigator or delegated investigator. Data will be entered into the eCRF using an access-controlled, GCP compliant, validated and audit-trailed system by authorized staff of the investigational site. Plausibility of the data will be checked as implemented in the CRF. Entered data will be monitored on a regular basis.. Implausible data and missing data will be queried. The database will be locked after completion of entry, cleaning of data and final data review. All relevant trial data and documents (CRF-worksheets, source data and Investigator Site File (ISF) including subject identification list and relevant correspondence) will be archived by the principle investigators for 10 years according to local law or regulations.

### Confidentiality {27}

All data will be handled in accordance to the European General Data Protection Regulation and the applicable local data protection regulations as well as the applicable regulations for the clinical trial. Subjects will be informed about data safety in the trial and have to give written consent to collect and process their data as well as to the transfer of their data in a pseudonymous way. The privacy policy has been reviewed by the responsible ethics committee. Data capture records, trial reports and communications and drug accountability records identifies the patient by an assigned identity number to maintain privacy. It must be determined by the principle investigators who is authorized to view personal data. The Patient Identification Log can be accessed only by the authorized study personnel. To prevent unauthorized access (electronically and physically) restricted access rights to pseudonymized data are implemented. All data will be stored either paper-based or electronically in a pseudonymous manner and handled strictly confidential. Data will be processed at the investigation site in accordance to the safety concept of the institution. Extensive back‐up procedures are implemented to strictly avoid loss of data. All legal requirements that concern data protection and data confidentiality will be respected thoroughly. Every authorized person is sworn to secrecy. Data of withdrawn patients will be stored and further used subjected to the patient’s consent. Data that is no longer used will be deleted immediately.. After the end of the archiving period, all data will be deleted according to data protection law.

### Plans for collection, laboratory evaluation and storage of biological specimens for genetic or molecular analysis in this trial/future use {33}

Not applicable, no samples collected.

## Statistical methods

### Methods and analyses {20a, 20b, 20c, 21b}

The primary population is the intent‐to‐treat population. This population is defined as all randomized patients with Baseline measurement of the primary endpoint (inclusion criterium). The primary analysis will be done as Baseline‐adjusted analysis of covariance, adjusted for study center with a type 1 error of 0.05 (two‐sided for pairwise comparisons) with primary endpoint FMA‐UE measured at the last therapy visit. The study arm will be coded as a three level factor and in the first step an F‐Test for the overall null hypothesis (all three means are equal) vs. the alternative (at least two measures are different) will be done. If this test is significant, all three pairwise comparisons will be performed without correction for multiple testing. If the F‐Test is not significant, p‐values for pairwise comparisons will be calculated but have to be interpreted descriptively. In the case of a significant result (for the F‐Test) in this step, following the principle of testing hierarchically ordered hypotheses, the same strategy will be applied for follow‐up after three months. For the parameters of interest (effects within study arms and their differences between study arms) two‐sided 95% confidence limits will be calculated. In case of relevant imbalances between study arms regarding known prognostic factors, sensitivity analyses will be done adjusted for these factors. Analogous methods will be applied for the analysis of secondary endpoints (proportional odds model for ordinally scaled variables, logistic regression for binary variables, if possible baseline adjusted). Even though p‐values will be reported, all results have to be interpreted descriptively. Descriptive analyses will include means, standard deviations, and ranges for continuous normally distributed data. Medians and interquartile ranges will be calculated for non‐normally distributed data. Nominal, especially binary variables will be described using absolute and relative frequencies. Additionally, we will present line listings for AEs/SAEs. Missing values of primary and secondary endpoints will be imputed multiply using the method of Rubin. Predictor variables will be age (years), gender, study center and Baseline, which will be available in the intent‐to‐treat population (inclusion criterion). We will use 500 imputation samples; the seed will be the calendarial date of the first programming of the analysis program. An interims analysis is not planned. Exploratory subgroup analyses will be done for gender. Before breaking the code of the randomization a statistical analysis plan will be produced. Deviations from this plan will be documented and justified.. In case of premature termination of study centers or severe imbalance of prognostic factors between study centers, a sensitivity analysis non‐stratified for study centers will be presented.

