## Interventions

### Intervention description {11a}

High‐frequency rTMS will be applied to the ipsilesional motor cortex in 400 bursts of 100 Hz triplets with a mean inter‐burst interval of 3 s (20 min treatment duration, 1,200 pulses per day) for five consecutive workdays (6,000 pulses total), followed by 40 min task‐specific hand/arm‐physiotherapy. The physiotherapy will be applied at all study centers according to a uniform standard operating procedure, which is based on standard treatment procedures in stroke care. Stimulation will be provided in a dedicated room by a GCP‐qualified trial physician or trial technician under supervision of a medical doctor. For the primary endpoint, FMA-UE raters will be trained to improve inter-rater reliability.

This trial has one Experimental Condition and the Control Conditions 1 and 2. The three conditions will be randomized 1:1:1. All conditions target the hand representation of the ipsilesional motor cortex.

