### Study visit procedures

#### Screening visit

Screening (V1) will be performed within maximal 14 days prior to first treatment (V2). After having signed the informed consent, patients will undergo all assessments listed below:- Physical and neurological examination and medical history. This includes documentation of the NIHSS, stroke lesion size and site, and major medical complications (e.g. pneumonia).- Clinical Assessments and Tests:◦ FMA‐UE; assessment at screening should be repeated within 3 days prior first treatment (V2), if the screening visit was done earlier◦ Relative grip strength measurement (vigorimeter) of the affected compared to the non‐affected hand. The best of 3 attempts will be documented; assessment at screening should be repeated within 3 days prior first treatment (V2), if the screening visit was done earlier.◦ Stroke‐specific Quality‐of‐Life Scale (SS‐QOL)◦ Modified Rankin Scale Score◦ Barthel Index- EEG measurement (to be repeated within 3 days prior first treatment (V2), if the screening visit was done earlier):◦ Preparation of 32‐channel EEG. Recording of a 5 min resting‐state eyes‐open EEG and subsequent analysis of the signal‐to‐noise (SNR) ratio of the peak of the µ‐oscillation (frequency band 7‐12 Hz) over the ipsilesional sensorimotor area in the C3 (stroke in the left hemisphere) or C4 (stroke in the right hemisphere)‐Hjorth montage.◦ Exclusion of subjects with an insufficient SNR of the sensorimotor µ‐rhythm below 3 dB◦ If applicable a diagnostic EEG measurement can be obtained to screen for abnormal EEG activity (e.g., interictal epileptic discharges) prior to treatment (not relevant for inclusion, sufficient data of one standard EEG can also be obtained from an EEG before screening).- TMS measurement (to be repeated within 3 days prior first treatment (V2), if the screening visit was done earlier):◦ Determination of the TMS hotspot over the hand representation of the ipsilesional motor cortex for eliciting MEPs of maximum amplitude in the first dorsal interosseus muscle of the paretic hand [please cite [22]].◦ Extended MEP search procedure (only in case if no MEPs can be obtained with standard single-pulse TMS in the resting muscle): MEP search during isometric tonic contraction of 10–20% maximum voluntary contraction (MVC) of the first dorsal interosseus muscle of the paretic hand.◦ If no MEPs can be obtained during contraction, MEP search with TMS double pulses (interstimulus interval (ISI) of 15 ms [16]) will be applied in the resting target muscle.◦ If still no MEPs can be obtained, TMS double pulses will be applied during isometric contraction.◦ If no MEPs can be obtained, the MEP search procedure can be repeated later up to 14 days after stroke onset.◦ If still no MEPs can be obtained after 14 days, the patient will be excluded.◦ Otherwise, the resting or active motor threshold in the first dorsal interosseus muscle of the paretic hand will be determined with the method that elicited MEPs. The motor threshold is defined in the resting muscle as the lowest TMS stimulator intensity that results in small MEPs > 50 µV peak-to-peak amplitude in > 5/10 trials. In the active muscle it is the lowest TMS stimulator intensity that results in MEPs > 200 µV in the average of 5 trials [22]. Motor threshold will be expressed as percentage of maximum stimulator output (%MSO).- Neuroimaging session procedures for measurement of anatomical MRI◦ In case the patient has already received a diagnostic MRI scan between onset of stroke and participation in the study, an additional anatomical MRI is required only if the diagnostic MRI scan in not suitable for the navigation system to guide TMS.◦ If the patient has not yet received an MRI between the onset of stroke and participation in the study or the existing MRI is not sufficient, an anatomical MRI (MPRAGE sequence, TE = 2.18 ms, TR = 2300 ms, TI = 1100 ms, flip angle = 9°, 192 slices, voxel size = 1 × 1 × 1 mm, DWI, FLAIR) should be obtained.◦ In the case of MRI contraindications TMS will be applied at the location of the identified hand motor hotspot. Neuronavigation (Localite GmbH) based on MNI‐brain adaption will then be employed to maintain a consistent coil position, orientation and angulation throughout the sessions of a given patient using skull and facial landmarks rather than the anatomical MRI data.- Randomization and Stratification: At the end of the screening visit and after checking all inclusion and exclusion criteria, the eligible study participants will be assigned to their respective treatment by randomization.◦ 1:1:1 randomization by biostatistical center◦ stratification will be applied with regard to:**▪** study center**▪** motor threshold (<60 %; >60 % MSO)

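### Motor threshold is a stated randomization stratum but is left out of the primary ANCOVA and the imputation model, and the strata are described inconsistently

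*Protocol article*

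**What the plan says.** **Randomization.** The section on sequence generation says that patients are "stratified according to study center and motor threshold (≤ 60%; > 60%MSO"). Its next sentence describes the list that the biostatistical center produced as block randomized "with varying block length and stratified for study center to realize a 1:1:1 randomization", with no mention of motor threshold. The screening visit section also names center and motor threshold as the two factors, but gives the second as "motor threshold (<60 %; >60 % MSO").

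**Primary analysis.** The statistical methods section sets a baseline-adjusted "analysis of covariance, adjusted for study center with a type 1 error of 0.05" (two-sided for pairwise comparisons), with FMA-UE at the last therapy visit as the endpoint. An overall F-test on the three arms comes first. The inferential pairwise comparisons and the three-month test follow only if it is significant.

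**Imputation.** The listed predictors are age, gender, study center and baseline.

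**Sample size.** The allowance for degrees of freedom names center and baseline, not motor threshold.

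**Further adjustment.** The only other route is a sensitivity analysis: "In case of relevant imbalances between study arms regarding known prognostic factors", the analysis is repeated with adjustment for those factors.

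**The concern.** An analysis normally carries the factors on which randomization was stratified. Stratifying makes the arms alike on the factor. If the model then leaves the factor out, the variation between its levels stays in the error term, although it no longer contributes to differences between arms. The estimated standard error is then too large, and the test rejects less often than its nominal level under the null. This holds only as far as the factor predicts the outcome after baseline adjustment.

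The omission is not simply detail left to the analysis plan. The article lists its covariates, its imputation predictors and its degrees-of-freedom allowance, and motor threshold is in none of them. The imbalance-triggered sensitivity analysis is unlikely to fill the gap, because stratification is there to prevent that imbalance.

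Power on the F-test is at stake. It is planned at about 80% and controls access to every later inferential comparison. The unclear strata raise a separate problem: a reader cannot tell which design the analysis should follow.

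**Working it through.** **Inputs from the sample size section.** Effect sizes of 0.67 (experimental against sham) and 0.335 (non-personalized, worst case); R² of 0.2 for baseline FMA-UE; 36 evaluable per arm; type 1 error 0.05; F-test power 80%; pairwise power 88%; 20% dropout. The recruitment section gives six sites, hence 5 degrees of freedom for center.

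**Assumption.** The article gives no prognostic value for motor threshold. Let e be the share of total outcome variance that the two-level stratum explains beyond baseline. The range used is 0 to 0.10.

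**Step 1: reproduce the plan.** Take arm means of 0, 0.335 and 0.67 SD and a residual variance of 1 − 0.2 = 0.8. The squared deviations from the overall mean sum to 2 × 0.335² = 0.22445.
- F-test noncentrality: 36 × 0.22445 / 0.8 = 10.10. With one covariate, power is 80.8% at 36 per arm and 79.5% at 35, so 36 is right.
- Pairwise noncentrality at 0.67: 0.67 / √(2 × 0.8 / 36) = 3.18. Power is 88.0% with two-arm degrees of freedom and 88.3% with pooled ones, against the stated 88%.
- Dropout: 108 / 0.8 = 135. The planned 144 leaves 9 more for degrees of freedom.

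**Step 2: add the stratum.** Residual variance becomes 0.8 − e. Error degrees of freedom fall from 108 − 3 − 6 = 99 (center 5, baseline 1) to 98. The F-test noncentrality becomes 8.08 / (0.8 − e), and the standard error changes by the factor √((0.8 − e)/0.8).

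| Extra R² (assumed) | Fall in SE | F-test power with stratum (without: 80.7%) | Pairwise power at 0.67 with stratum (without: 88.2%) | n per arm for 80% F-test power (without: 36) |
|---|---|---|---|---|
| 0 | 0% | 80.7% | 88.2% | 36 |
| 0.02 | 1.3% | 81.7% | 89.0% | 35 |
| 0.05 | 3.2% | 83.3% | 90.2% | 34 |
| 0.10 | 6.5% | 85.9% | 92.0% | 32 |

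At e = 0 the extra degree of freedom costs less than 0.1 point of power.

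**Step 3: type I error by simulation.** 10,000 runs per setting, 108 patients, six centers, two motor-threshold strata assumed equal in size, blocks of 3 or 6 within center by stratum, no treatment effect.

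| Extra R² (assumed) | F-test rejection rate, stratum omitted | Stratum included |
|---|---|---|
| 0 | 0.053 | 0.053 |
| 0.02 | 0.049 | 0.052 |
| 0.05 | 0.043 | 0.053 |
| 0.10 | 0.033 | 0.049 |

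The Monte Carlo standard error near 0.05 is √(0.05 × 0.95 / 10,000) = 0.002. Omission makes the test conservative as e grows and never inflates it.

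**Step 4: compare the descriptions of the strata.**
- *Cut point.* The screening visit section has below 60 and above 60, so a threshold of exactly 60% belongs to neither stratum. The sequence generation section has at most 60 and above 60, which covers every value.
- *Factors.* Sequence generation names two factors in one sentence and only center in the next.

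These conflicts need no assumption, and they do not enter the power figures above.

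**The case against.** **No shown loss.** No section says that motor threshold predicts FMA-UE beyond baseline. If it does not, power is the same with or without it. This stands. A reader might infer that precision is certainly being lost, but the documents support only a conditional statement.

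**Validity is intact.** The planned power is reached without motor threshold, the degrees-of-freedom allowance agrees with the stated model, and the trial calls itself exploratory. This also stands: the point concerns efficiency and agreement between design and analysis.

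**The strata conflict may be editorial.** The sentence naming center does not say that center is the only factor, and the article is condensed. That is possible, but the text does not settle it, and the cut-point mismatch is plain. A reader might also infer that the conflict itself costs power. It does not; it leaves unclear what was stratified.

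**Center-only list.** A reader might infer that motor threshold would then be unbalanced by design. That is wrong: 1:1:1 randomization still balances it in expectation, and only the exact balance is left to chance. The stated model would then match the randomization, and the complaint about an omitted stratum would fall away.

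**Wider changes.** One might also want time since stroke onset as a covariate, or the imbalance-triggered analyses dropped. The documents give no prognostic figure for the former, and the latter are labelled as sensitivity analyses and do no harm to the primary result. Neither change is part of this point.

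**Conclusion.** The point holds as a modest, conditional one. As written, the primary model and the imputation model leave out one of the two stated stratification factors. If motor threshold explains an assumed 2% to 10% of outcome variance beyond baseline, including it would raise F-test power by 1.0 to 5.2 points (81.7 − 80.7 and 85.9 − 80.7) and pairwise power at 0.67 SD by 0.8 to 3.8 points. With the stratum omitted, simulated type I error falls to about 0.033 at the top of that range. If motor threshold explains nothing, nothing is gained and practically nothing is spent.

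There is no bias and no type I error inflation, and the stated 36 per arm, 88% and 144 are unaffected. The inconsistent cut point and the two descriptions of the list are textual faults that need reconciling whatever the prognostic value is.

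**What to change.** 1. Confirm from the randomization list which factors and which cut point it uses, including where a threshold of exactly 60% was placed. State them identically in the screening visit and sequence generation sections.
2. Add the motor-threshold stratum, as used in the list, as a fixed factor in the primary ANCOVA and as a predictor in the imputation model. If the list proves to be stratified by center only, correct the description; motor threshold is then an optional prespecified covariate rather than an omitted stratum.
3. Keep the planned imbalance-triggered sensitivity analyses.

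The cost is wording and one degree of freedom (less than 0.1 point of power). The article commits to an analysis plan before the randomization code is broken, so the change can be made there while the data are still blinded.
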